# PROTOCOL SUMMARY

***Sponsor*** Centre Médical Jérôme Lejeune

***Active agent***  Calcium salt of folinic acid, pentahydrated

***Title*** Phase II-III clinical trial of one year's duration, carried out as a double-blind placebo-controlled study in two parallel groups, with evaluation of the effects of folinic acid (1 mg/kg/day) on cognitive function in young children with Down's syndrome. ENTRAIN — a phase II-III trial with direct individual benefit.

***Co-ordinator*** [name] [name]

***Study centre*** Centre Médical Jérôme Lejeune
[name] Tel. [contact]
[name] Fax [contact]

***Start date of the trial*** January 2000

***Phase and duration of the trial*** Phase II-III study to confirm efficacy. Inclusion period of 1.5 years.

***Aims*** The principal aim of the study is to evaluate, in a double-blind, placebo-controlled study, the effects of folinic acid on cognitive function in young children with Down's syndrome. The secondary aims of this trial are to evaluate the tolerance of this product in this population and to assess its possible effects on behavioural problems.

***Methodology*** Double-blind, placebo-controlled trial with two parallel groups.

***Number of subjects*** 100 (50 on folinic acid, 50 on placebo).

***Diagnosis, inclusion criteria*** We will include children with Down's syndrome in a stable state and old enough for assessment with the Brunet-Lezine test (revised version; 6 to 24 months), after obtaining written informed consent from the parents or guardians of these children, who must be resident in France and contactable by telephone. We will not include patients with a history of myeloproliferative syndrome, infantile seizures (current), or patients who have started thyroid treatment in the last three months or who are taking antifolic acid treatments (methotrexate, phenytoin). All patients presenting myeloproliferative syndrome or requiring thyroid treatment will be excluded from the trial.

***Treatment studied*** Folinic acid per os (Folinoral®) 1 mg/kg/d, or placebo, formulated as capsules.

***Evaluation criteria*** Principal criterion: change in developmental age (DA).
Secondary criteria: clinical and biological tolerance, opinion of the parents (concerning the continuation of treatment), opinion of the doctor and psychologist.

***Statistical methods*** Student's t tests (or Mann-Whitney U tests) for quantitative variables and 2 tests for qualitative variables. PCSM® (Deltasoft) and SPSS® software will be used, together with SAS if required.
Stratification will be carried out retrospectively, based on initial development quotient.

# ABBREVIATIONS AND DEFINITIONS

## AbBreviations

0 concerns the initial examination

DA developmental age

GCP good clinical practice

C consultation

CBS cystathionine -synthase

IRB institutional review board

CGI clinical global impression

CMJL Centre Médical Jérôme Lejeune

VAS visual analogue scale

f concerns the final examination

i  concerns an intermediate examination

I item

d day

kg kilogramme

mg milligramme

NA not applicable

ND not determined

CC cranial circumference

PO, po per os

SOP standardised operating procedure

DQ developmental quotient

IQ intellectual quotient

W week

SAM S-adenosyl methionine

SOD superoxide dismutase

t concerns intermediate telephone contacts

T21 trisomy 21 (Down's syndrome)

THF tetrahydrofolate

## DEfinitions

Folinic acid C20H23N7O7              Molecular mass: 491.5.

folinate, 5‑formyl tetrahydrofolic acid, 5‑formyl THF
N‑[[[(amino‑2 formyl‑5 hydroxy‑4 tetrahydro‑5,6,7,8 pteridinyl‑6)               methyl] amino]‑4 benzyl] L‑(+) glutamic acid.

Calcium folinate: pentahydrated calcium salt of folinic acid
C20H21CaN7O7.5H2O
Molecular mass: 601.6.

Folinoral® Pharmaceutical formulation used in this study. Its active ingredient is the pentahydrated calcium salt of folinic acid. The section from the Vidal guide concerning this product from Laboratoires Thérabel-Lucien Pharma is provided in the appendix.

Brunet-Lezine In this study, developmental age, the principal judgement criterion, is determined by means of the revised Brunet-Lezine test. This very standard test is distributed by EAP (Editions et Applications Psychologiques, [name]). It is described in the section dealing with judgement criteria and a sheet corresponding to this test is supplied in the appendix.

# BACKGROUND

Down's syndrome is a dysmorphic syndrome associated with mental retardation and is caused by trisomy of chromosome 21, detectable by karyotyping.

## GENERAL INFORMATION

Diseases caused by chromosomal abnormalities are unusual in that the genetic abnormality is purely quantitative — repetition of part of the information present on the chromosome in the case of trisomies. Several observations confirm the integrity and quality of the information contained in aneuploid genomes. In particular, half the children of mothers with Down's syndrome have the same trisomy as their mother, whereas the other half have a normal karyotype and 46 chromosomes. The normal phenotype of this second group of children demonstrates that the maternal chromosomes 21 are qualitatively normal and that the presence of two copies of this chromosome is sufficient to cause the disease in the other children.

Thus, trisomy leads to excessive protein synthesis rather than to the synthesis of abnormal proteins. Its effect is therefore one of gene dose. These metabolic abnormalities being quantitative rather than structural, treatment may be possible, as most drugs function precisely by modifying the rates of enzymatic reactions.

In addition, a foetus presenting several serious metabolic abnormalities is highly unlikely to survive, as in many cases a single serious abnormality is lethal in itself. For this reason, only a small number of the metabolic abnormalities associated with the 700 genes present on chromosome 21 need to be taken into account in Down's syndrome. Changes in the rate of only a handful of chemical reactions in the brain may make it possible to improve considerably the cognitive functions of patients with Down's syndrome.

Treatment is thus potentially possible.

## Down's syndrome

Down's syndrome is the most frequent cause of mental retardation, accounting for one third of all cases. The incidence of Down's syndrome is fairly stable and is of the order of one case in every 700 children. In Alsace, the incidence of Down's syndrome is one case per 1050 live births [[[1]](#endnote-2)]. Paradoxically, prenatal diagnosis has not led to a decrease in the number of births of children with Down's syndrome, which has indeed remained stable or even increased [[[2]](#endnote-3)]. Over the last 30 years, maternal age has increased consistently, and maternal age has clearly been identified as the most important risk factor [[[3]](#endnote-4),[[4]](#endnote-5),[[5]](#endnote-6)]. In 1930, children with Down's syndrome had a life expectancy of nine years; their life expectancy had increased to 55 years in 1986, and is undoubtedly now greater than 60 years. There are currently about 40,000 to 50,000 patients with this condition in France, and several million such patients worldwide. The socio-economic burden represented by these patients is considerable, because a non-negligible proportion of these patients are institutionalised (costing several hundreds of thousands of francs per year). An improvement, even if only slight, in the IQ of patients with Down's syndrome, might allow a larger proportion of these patients to find work and would increase their autonomy, allowing them to live independently, thereby greatly reducing health expenditure.

## Folates and down's syndrome

The principal role of folates in the body is to supply single-carbon radicals during transmethylation reactions. Many lines of evidence suggest that folates play a key role in the pathogenesis of mental retardation in patients with Down's syndrome:

- Macrocytosis in these patients
- The location of the reduced folate transporter gene (SLC19A1-hFOLT1) on chromosome 21
- The role of folates in two of the reactions of *de novo* purine synthesis, one of which depends directly on the product of the *GART* gene, which is also located on chromosome 21
- The role of the serine residue of folates in the remethylation of homocysteine to produce methionine. By contrast, the reaction to generate cystathionine involves the production of S-adenosyl methionine, which is catalysed by cystathionine ‑synthase, encoded by a gene on chromosome 21.
- The existence of a functional deficiency of acetylcholine, a neuromediator synthesised through folate-dependent methylation reactions.

All genetic diseases affecting folate metabolism are associated with low intelligence. In addition, many diseases associated with low intelligence are accompanied by genuine problems with monocarbon metabolism: sarcosinaemia, glycinaemia, homocysteinuria, hisidinaemia, carnosinuria, hyperprolinaemia, hyperhydroxyprolinaemia, iminodipeptiduria, Hartnup disease and Lesch-Nyhan syndrome.

In adults, folate deficiency causes recurrent haematological problems and infections, but may also cause neurological problems (polyneuropathies, restless leg syndrome), together with cognitive and psychiatric problems (depression, dementia); these disorders may be readily reversed by treatment [[[6]](#endnote-7)], confirming the important role of folates in the functioning of the central nervous system. However, adult patients may not display intra-erythrocyte folate deficiency or macrocytosis [[[7]](#endnote-8)]. Folate administration significantly improves the results obtained in Wechler's psychometric assessments of memory and IQ in patients with mental problems [[[8]](#endnote-9)].

The importance of folates in the development of the central nervous system is also clearly demonstrated by the key role of folate deficiency in neural tube malformation, with even minor deficiencies increasing the risk of such malformations [[[9]](#endnote-10)].

Conversely, the importance of folates in Down's syndrome is clearly demonstrated by the deleterious effects of drugs with antifolate activity in these patients: sulfamides (e.g. trimethoprime-sulfamethoxazole), antiepileptic drugs (phenytoin) and antimitotic agents.

An open initial clinical trial of folinic acid has been carried out using a cohort of 69 patients with Down's syndrome between the ages of 1 and 44 years. The inclusion and judgement criteria were psychotic disorders and Alzheimer-type dementia. This study demonstrated a beneficial effect of treatment in more than 50% of patients. No adverse effect was recorded, with the exception of one case of excitation, which regressed when the dose was decreased. The dose administered was between 0.15 mg/kg/d and 1.92 mg/kg/d. The dose regularly having a therapeutic effect was about 1.00 mg/kg/d. Confirmation is required, as there was no control group in this study, but the existence of a dose-dependence effect strongly suggests that this effect is real [[[10]](#endnote-11)].

All these elements are consistent with Down's syndrome patients having cerebral folate deficiency or displaying a defect in folate use in certain cells of the central nervous system. These problems may be closely related to the low intelligence of these patients, and their correction may improve cognitive function.

## folic and folinic acid

For higher function problems, such as psychoses, folinic acid has been shown to be more effective than folic acid for the administration of folates. There are several reasons for this: it is more stable, its digestive absorption is greater, it has a longer half-life and it crosses the blood-brain barrier more readily. Indeed, folic acid cannot pass from the blood into the central nervous system without prior transformation and is eliminated by an active transport system [[[11]](#endnote-12),[[12]](#endnote-13)].

## Conclusion

It would therefore seem necessary to test the hypothesis that folates may affect the cognitive functions of patients with Down's syndrome, under certain conditions:

- The product used should be folinic acid, which is the most likely to be effective. It should be used at a sufficiently high dose to ensure that any effect is detectable;
- The study should be rigorous in terms of its methodology (control group, double-blind, placebo-controlled etc.) and its quality (quality criteria recommended by GCP, use of standardised operating procedures, auditing etc.);
- The judgement criteria must be validated;
- Folinic acid is extremely well tolerated in general, but tolerance monitoring is required in this particular population;
- Finally, the detection of an effect on cognitive function will require the treatment of young children whose brains do not yet have developmental abnormalities too fixed and too irreversible for treatment and whose brains are still capable of growth and development.

# practical information

We provide here details of the people involved in this trial and the site at which the research will take place. The *curriculum vitae* of the participants are provided in the appendix.

# aims

The principal aim of this phase II-III trial with direct individual benefit, ENTRAIN, is to carry out a double-blind, placebo-controlled evaluation of the effects of folinic acid on cognitive function in young children with Down's syndrome.

The secondary aims of this trial are to evaluate the tolerance of this product in this defined population and to assess its possible effects on behavioural problems.

# design of the trial

## summary

The chronology of the trial is summarised below in table form.

|  | Initial consult | Bimonthly contacts | Intermediate consult | Final consult |
| --- | --- | --- | --- | --- |
|  | C0 | Ct | C1 | C2 |
| **Date** | 0 months |  | 6 months | 12 months |
| **General** |  |  |  |  |
| Information of the parents | **+** | - | - | - |
| Consent | **+** | - | - | - |
| Inclusion criteria | **+** | - | - | - |
| Non-inclusion criteria | **+** | - | - | - |
| History | **+** | - | - | - |
| **Clinical examination** |  |  |  |  |
| Medical examination | **+** | * | **+** | **+** |
| Height-weight-CC | **+** | - | **+** | **+** |
| Doctor's opinion (CGI) | - | - | **+** | **+** |
| Psychologist's opinion (VAS) | - | - | **+** | **+** |
| Brunet-Lézine Test | **+** | - | **+** | **+** |
| Parents' opinion of treatment | - | - | **+** | **+** |
| **Biological tests** |  |  |  |  |
| Blood formula | **+** | * | **+** | **+** |
| Thyroid assessement | **+** | * | **+** | **+** |
| Iron, Ferritin | **+** | * | + | + |
| Adverse effects | **+** | + | + | + |
| Date of the next visit | **+** | + | + | - |

* only if required

## trial description and chronology

The total duration of follow-up for any given patient in the trial will be 1 year ± 30 days.

The first medical consultation will include:

- Information about the trial and the signing of the consent form;
- Confirmation of the diagnosis, checking for the presence of karyotyping data in the patient's medical records;
- Checking the inclusion and non-inclusion criteria, including, in particular, ability to undergo the revised Brunet-Lezine test for determining developmental age (DA);
- A general clinical and neurological examination, with measurement of height, weight and CC;
- Prescription of routine biological tests (blood formula, iron, ferritin, thyroid assessment) and other specific examinations, if necessary.

The first consultation with the psychologist will include a psychological examination and the revised Brunet-Lezine test.

Intermediate contact will be made with the parents at intervals of no more than two months. During these intermediate contacts by telephone, the interview by a doctor from the CMJL will focus particularly on the tolerance of folinic acid treatment.

If necessary, the final consultation may take place early, in cases of withdrawal from the study.

The intermediate consultation (6 months ± 15 days) and the final visit (1 year ± 30 days) will include:

- A general clinical and neurological examination, with measurement of height, weight and CC;

- The recording of any adverse events;

- The recording of the doctor's opinion concerning the child (CGI);

- The recording of the overall opinion of the psychologist concerning the development and behaviour of the child on a visual analogue scale (VAS);

- The revised Brunet-Lezine test (determination of DA);

- The recording of the parents' opinion on the treatment of the child;

- The prescription of routine biological tests (blood formula, iron, ferritin, thyroid assessment) and other specific examinations if required.

The entire study will therefore include only standard examinations: three medical examinations, three psychological examinations and three sets of standard biological tests. Between consultations, three to five telephone contacts are planned to help the family and for the monitoring of tolerance and compliance with treatment. If possible, all the examinations will take place on the same day, with the same doctor and the same psychologist.

The total duration of the inclusion period will be 1.5 years.

# subject selection

Patients will be selected on the following criteria:

## inclusion criteria

Patients with the following characteristics will be included:

- Down's syndrome (free and homogeneous trisomy 21),

- Suitability for assessment with the revised Brunet-Lezine test at the time of the first examination and (predictively) the second examination. Children should thus be aged between about six and 24 months,

- Weight between 6 and 26 kg,

- Planned stable maintenance treatment for the next year,

- Good compliance likely and possibility of carrying out subsequent examinations within the required time frame,

- Patient resident in France

- Parent or guardian of the child contactable by telephone,

- Parent or guardian having received and understood the information document and signed the informed consent form.

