### Efficacy

Efficacy will be evaluated using several criteria.

The principal evaluation criterion will be the change in developmental age, the profile of which is known for patients with Down's syndrome [[[16]](#endnote-16)]:

Translation for the figure: Age mental = mental age; Age reel = real age.

Developmental age will be assessed by the revised Brunet-Lezine test administered before (DA0) and after (DAf) treatment: (DAf - DA0). The revised Brunet-Lezine test is widely recognised as a test for the evaluation of psychomotor development in infants. It has been validated and its metrological qualities (sensitivity, fidelity-homogeneity, dispersion and validity, including for Down's syndrome children) are well known. For further information about this test, please consult reference 13.

The other criteria for efficacy evaluation will be:

- CGI, as recorded by the doctor;
- A score for psychologist satisfaction, estimated on a VAS, evaluating the opinion of the psychologist on the subjective improvement of the child since the start of treatment.
- The response of the parents to the question "If possible, would you like to continue this treatment ?" The response will be scored as follows: in favour of continuing treatment/against continuing treatment/does not know or no opinion expressed.

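### The entry rule requires Brunet-Lezine testability only up to the second (6-month) examination, but the primary endpoint is taken at the third (12-month) examination

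*Protocol*

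**What the plan says.** The inclusion criteria in the protocol's subject selection section ask that the child be suitable for the revised Brunet-Lezine test "at the time of the first examination and (predictively) the second examination". The age window is presented as a consequence of that rule: "Children should thus be aged between about six and 24 months".

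The trial description and chronology section counts "three medical examinations, three psychological examinations and three sets of standard biological tests". It times the two later visits in these words: "The intermediate consultation (6 months ± 15 days) and the final visit (1 year ± 30 days) will include" (the list of procedures that follows contains the Brunet-Lezine test). The summary table in the design section shows the test at C0, C1 and C2, that is at 0, 6 and 12 months.

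The Efficacy section defines the primary criterion as DAf − DA0, from the test "administered before (DA0) and after (DAf) treatment". The abbreviations list says that the suffix f refers to the final examination.

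The Protocol Summary puts "revised version; 6 to 24 months" in brackets after the name of the test. It does not say whether this is the scored range of the test or the age of the children at entry.

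**The concern.** The criterion exists so that a child who enters can be measured when it counts. On the protocol's own count the second examination is the 6-month one, so the rule covers baseline and mid-trial but not the visit that yields DAf. A child entering at 24 months is about 30 months old at the second examination and about 36 months old at the final one.

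No other entry rule fills the gap. The criterion on being able to carry out later examinations in time concerns attendance. The check of ability to take the test belongs to the first consultation. The missing-data section deals with a child who does not return, not with one who returns and has reached the top of the scale.

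If some children reach the top of the test by 12 months, their gain is recorded as smaller than it is. With a real treatment effect this happens more often in the arm with the larger gain, so the observed difference shrinks and power falls. Because eligibility is fixed at enrolment, the analysis cannot repair this later.

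**Working it through.** **Inputs from the protocol** (number of cases section): one-year gain 0.666 years on placebo (8.0 months) and 0.900 years on folinic acid (10.8 months); SD 0.4 years (4.8 months); two-sided alpha 0.05; power 80%; 47 per group required, 50 recruited. Entry age is about 6 to 24 months.

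**Assumptions not in the protocol:** developmental age (DA) at entry equals 0.666 × age; entry ages are uniform over 6–24 months; between-child SD of baseline DA is 0, 2 or 4 months; the test ceiling is a DA of 24, 30 or 36 months.

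**Step 1: the stated sample size.** Difference 0.900 − 0.666 = 0.234 years; standardised 0.234/0.4 = 0.585. The normal approximation gives 46 per group. The exact t test gives 46.85, so 47, as stated. Exact power is 80.1% at 47 and 82.5% at 50 per group. The sample size calculation is not in error on this point.

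**Step 2: the oldest entrant at each examination.** At 24 months, DA0 = 0.666 × 24 = 16.0 months.
- At 6 months, with half the annual gain: 16.0 + 4.0 = 20.0 (placebo) or 16.0 + 5.4 = 21.4 (folinic acid).
- At 12 months: 16.0 + 8.0 = 24.0 or 16.0 + 10.8 = 26.8.

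Under a 24-month ceiling this child is expected to satisfy the rule at the second examination and to be at or past the ceiling at the primary one.

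**Step 3: capping for that child.** For final DA normal with mean μ and SD σ = 4.8, ceiling c and z = (c − μ)/σ, the expected recorded value is μΦ(z) − σφ(z) + c(1 − Φ(z)), and the chance of exceeding the ceiling is 1 − Φ(z). For c = 24:
- placebo: z = 0, recorded mean 24 − 4.8 × 0.399 = 22.09;
- folinic acid: z = (24 − 26.8)/4.8 = −0.583, recorded mean 23.17.

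The recorded difference is 23.17 − 22.09 = 1.08 months, against a true 2.8.

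| Assumed ceiling (months) | Chance above ceiling, placebo / folinic acid | Share of true difference kept |
|---|---|---|
| 24 | 50% / 72% | 39% |
| 30 | 11% / 25% | 83% |
| 36 | 0.6% / 2.8% | 99% |

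**Step 4: the whole trial.** Simulated trials of 50 per group, with DA capped at the ceiling. Ranges run over the three baseline SDs.

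| Assumed ceiling (months) | Above ceiling, placebo / folinic acid | Mean difference (years) | Power |
|---|---|---|---|
| 24 | 16–20% / 30–33% | 0.17–0.18 | 68–76% |
| 30 | 2–5% / 6–10% | 0.215–0.226 | 79–82% |
| 36 | 0.1–0.6% / 0.4–1.6% | 0.232–0.234 | 82–83% |
| none | – | 0.233–0.234 | 82–83% |

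Simulation error on a power near 80% with 4,000 trials is √(0.8 × 0.2/4000) = 0.6 percentage points.

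**The case against.** **The ceiling is not in the protocol.** The size of the harm rests on it. A reader might infer from the bracketed 6 to 24 months in the summary that the test stops at 24 months, and so that the primary endpoint is bound to be truncated. The text does not support this. The inclusion criteria give the same range as the age at entry, and the test scores developmental age, which for the oldest entrants is expected to be about 24–27 months at the end, not 36. This objection stands: truncation is a possibility to be checked, not an established fault.

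**The per-child figures describe an extreme.** They apply to the oldest possible entrant, and the trial-wide loss is much smaller. More advanced children would lose more, but the present rule already screens some of them. At an assumed developmental quotient of 0.80, a 24-month-old has DA0 = 19.2 and an expected 6-month value of 19.2 + 5.4 = 24.6 on folinic acid, already above a 24-month ceiling. This also stands, so the trial-wide figures are the ones to use.

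**The wording may mean a before-and-after pair.** In a translated protocol, the second examination could be the post-treatment test. The protocol's count of three psychological examinations weighs against that reading. If it was intended, an investigator applying the text could still screen only to 6 months, so the wording needs correcting either way.

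**Other protection.** The age limit does restrict developmental age at 12 months indirectly, and the Efficacy section says the test's metrological properties are known, including in children with Down's syndrome. Neither shows that the range suffices at 12 months.

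**The bias is conservative.** A cap common to two randomised, blinded arms costs power and does not favour folinic acid. That is correct and limits the severity.

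**Conclusion.** The mismatch is in the operative text: predicted testability is required to the second of three examinations, and the primary endpoint uses the third. The consequence is conditional. With a ceiling near a DA of 24 months, the difference would shrink from 0.234 to about 0.17–0.18 years, and power at 50 per group would fall from about 82% to about 68–76%. At 30 months the loss is small, and at 36 months negligible. These figures rest on the assumed entry-age distribution, baseline developmental ages and ceilings; only the gains, SD and group size are the protocol's own.

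A reader might go further and conclude that the trial is underpowered or the sample size wrong. Neither follows: the 47 per group reproduces, and power suffers materially only under a ceiling that the protocol does not establish. Severity is minor to moderate.

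**What to change.** In the inclusion criteria, replace the reference to the second examination with the final (12-month) examination. Then confirm, against the scored upper limit of the revised Brunet-Lezine test, that a 24-month entry age meets the amended criterion. Change the age limit only if it does not.

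I would not add a rule that DA0 plus the planned 10.8-month gain must lie below the ceiling. It protects only the mean: a child admitted at that boundary still has about a 50% chance of exceeding the ceiling on folinic acid. Under a 24-month ceiling it would require DA0 ≤ 24 − 10.8 = 13.2, that is age ≤ 13.2/0.666 = 19.8 months, removing (24 − 19.8)/18 = 23% of the entry span. That is a real recruitment cost in one centre with a 1.5-year inclusion period.

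The cost of the recommended change is one amended phrase and one look-up. A few of the oldest or most advanced children may become ineligible, and more if the look-up forces a lower age limit. No stated sample size figure changes.
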